#### Secondary outcomes

Secondary outcomes are as follows:
Chemotherapy adherence: The percentage of patients who completed the full-course chemotherapy in a standard dose. If only the full course of treatment is completed but the dose of chemotherapy is reduced, or the dose is unchanged but the course of treatment is shortened, the case will be treated as poor adherence.Stratified analysis: Subgroup analysis will be done according to age, chemotherapy regimen, and chemotherapy strategy.Adverse events: Any toxic side effects such as general condition, gastrointestinal reactions, liver and kidney function, skin reactions, burns, and heat syndrome will be recorded.ECOG PS: The performance status of the patients before and after the completion of the whole treatment cycle according to the Eastern Cooperative Oncology Group.Quality-of-life survey: EORTC QLQ-C30 (V3.0) and EORTC QLQ-BR23 will be used to assess the QoL of patients. QLQ-C30 is a scale developed by the European Organization for Research and Treatment of Cancer (EORTC) to measure the QoL of cancer patients. QLQ-BR23 is a QoL questionnaire designed for breast cancer patients, which is suitable for evaluating all breast cancer patients regardless of the type of treatments. Also, a TCM Constitution survey based on the judgement criteria recognized by the China Association of Chinese Medicine will be conducted [28]. The TCM Constitution is assessed by filling out the “the Criteria of Classification and Judgment of TCM Constitution (ZYYXH/T157-2009)” (Table 1). Every patient is designed to respond to the questionnaire three times: (1) before chemotherapy initiation, (2) during mid-term chemotherapy, and (3) before the last cycle of chemotherapy. All assessments will be completed the day before chemotherapy administration.Survival: The differences in 3-year DFS and OS between the treatment group and the control group will be analysed.

**Table 1 Tab1:** “The Criteria of Classification and Judgment of TCM Constitution” scale

Classification	Conditions	Judgement
Normal constitution	A conversion score of ≥ 60, and conversion score of < 30 in all other 8 types	Yes
	A conversion score of ≥ 60, and conversion score of < 40 in all other 8 types	Generally yes
	Unsatisfied for the above conditions	No
Abnormal constitution	A conversion score of ≥ 40	Yes
	A conversion score of 30 to 39	Likely yes
	A conversion score of< 30	No

The scale consists of 9 types including constitution of Gentleness (type A), Qi-deficiency (type B), Yang-deficiency (type C), Yin-deficiency (type D), Phlegm-wetness (type E), Wetness-heat (type F), Blood-stasis (G type), Qi-depression (H type), and Special diathesis (type I). Each type is graded in 5 contents. The original score is the sum of all items. Conversion score = [(original score − number of items)/(number of items × 4)] × 100

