## Introduction

### Background and rationale {6a}

Breast cancer is the most common malignant tumour in Chinese women, and its number of new cases and deaths accounts for 12.2% and 9.6% of the total globally [1]. Chemotherapy is one of the routine treatments for breast cancer [2–4]. For patients with early-stage breast cancer, dose-densed anthracycline combined with taxane regimens [5–7] or high-intensity chemotherapy [8, 9] is often recommended, yet such a combination regimen can cause acute cytotoxicity. While inhibiting tumour cell growth, it also kills haematopoietic cells and leads to significant myelosuppression, especially neutrophils [10]. Chemotherapy-induced myelosuppression (CIM) could lead to febrile neutropenia (FN), increase the risk of infection, and affect the survival of patients and thus usually results in the reduction in dose or even discontinuation of chemotherapy [11]. Therefore, the prevention and treatment of CIM are critical in breast cancer management.

At present, recombinant human granulocyte colony-stimulating factor (rhG-CSF) is commonly used in the prophylactic and therapeutic treatment of CIM [12–14]. rhG-CSF is a synthetic cytokine that promotes the proliferation, differentiation, and activation of neutrophils, mainly used for treating neutropenia after cytotoxic chemotherapy. rhG-CSF can significantly reduce the incidence of FN, shorten hospital stay, and reduce the use of intravenous antibiotics without affecting the efficacy of anti-tumour therapy [15, 16]. Prophylactic use of rhG-CSF is considered in patients with dosing reduction or delayed chemotherapy which may lead to an unfavourable prognosis [17–19]. Although the short-term effect of rhG-CSF is prominent, its rapid white blood cell boosting effect does not last long. Also, it may cause side effects such as bone pain, fever, spleen rupture, myelodysplastic syndrome (MDS), and acute myeloid leukaemia (AML) [20–23], which seriously upset the quality-of-life (QoL) and life expectancy of patients.

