#### Chemotherapy regimen

The investigator is responsible to decide whether adjuvant chemotherapy or neoadjuvant chemotherapy is suitable for the patients according to the CACA Guidelines for Breast Cancer Diagnosis and Treatment (2015 Edition) and NCCN Clinical Practice Guidelines in Oncology: Breast Cancer (Version 3. 2015). Choices of chemotherapy regimens include anthracycline (EC × 4 times, CEF × 6 times), taxanes (TC × 4–6 times, P × 4–6 times), anthracycline combined taxanes (TAC × 6 times, FEC × 3 followed by T × 3 times, AC × 4 followed by T × 4 times, AC × 4 followed by wP × 12 times, ddAC × 4 followed by wP × 12 times), and others (PC × 4–6 times, DP × 4–6 times, NX × 4–6 times, X × 4–6 times).

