#### Short-term efficacy

Blood routine test: Monitoring WBC count and ANC once a week during every cycle of chemotherapy.TCM-related symptom: The investigators will evaluate the TCM-related symptoms based on the scoring method (Table 3) described in “Chinese Medicine New Drug Clinical Research Guidelines (Trial)” (China Medical Science and Technology Press, 2002) every 3 months.Adverse effects: Grading on a scale of 0 to 4 according to CTCAE 4.0.2.Quality-of-life: EORTC QLQ-C30, QLQ-BR23, and TCM Constitution.

**Table 3 Tab3:** Schedule of enrolment and assessment

	Baseline	During chemotherapy (every cycle)	Follow-up after chemotherapy (month)				
	0	1–8	6	12	18	24	36
Enrolment							
Informed consent	√						
Eligibility	√						
General assessment							
Age	√						
Sex	√						
Height	√						
Weight	√	√					
Body surface area	√						
Surgical approach	√						
Chemotherapy regimen	√						
Chemotherapy strategy	√						
Pathological stage	√						
Molecular subtype	√						
ECOG PS	√	√	√	√	√	√	√
EORTC QLQ-C30	√	√					
EORTC QLQ-BR23	√	√					
TCM constitution	√	√					
Chest CT	√			√		√	√
*Breast MRI	√			√		√	√
Serum tumour biomarkers	√	√	√	√	√	√	√
Key evaluation							
Blood routine test	√	At least once per week	√	√	√	√	√
Safety examination							
Urine routine test	√	√	√	√	√	√	√
Liver function (ALT, AST, ALP, TBIL, GGT, etc.)	√	√	√	√	√	√	√
Kidney function (CR, BUN, SCR, UA, etc.)	√	√	√	√	√	√	√
Electrocardiogram	√	√	√	√	√	√	√
Adverse events		√	√	√	√	√	√
Data evaluation							
Audit medical records		√	√	√	√	√	√
Ombudsman reviews medical records		√	√	√	√	√	√
Outcome measures		√	√	√	√	√	√

*MRI assessments were conditionally performed according to the patient’s disease status

All results are recorded in the case report form. Participants who show any adverse effects will be reported and followed up by their responsible physicians.

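### The quality-of-life questionnaires have two conflicting schedules, and under the three-times schedule a patient who stops chemotherapy early has no final form

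*Protocol article*

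**What the plan says.** The Quality-of-life survey item under Secondary outcomes covers QLQ-C30, QLQ-BR23 and the TCM Constitution survey. It then fixes three questionnaire times for every patient: "1) before chemotherapy initiation, (2) during mid-term chemotherapy, and (3) before the last cycle of chemotherapy". It adds: "All assessments will be completed the day before chemotherapy administration".

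Table 3, under Short-term efficacy, ticks the same three instruments at baseline and in the column headed "During chemotherapy (every cycle)", numbered 1–8. It ticks none of them at months 6 to 36. Where a row follows another frequency, the table writes it out: the blood routine test row reads "At least once per week". The quality-of-life rows carry no such note.

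The article expects some patients to stop early. Background and rationale {6a} says that myelosuppression "usually results in the reduction in dose or even discontinuation of chemotherapy". The chemotherapy-adherence outcome provides for the case where "the dose is unchanged but the course of treatment is shortened, the case will be treated as poor adherence".

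Two sections deal with data after stopping. Criteria for discontinuing {11b} keeps outcome collection going as normal after dose reduction or discontinuation. Strategies to improve adherence {11c} ends it for participants who discontinue and withdraw.

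**The concern.** There are two linked problems.

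First, the text and the table give different numbers of forms for the same instruments. The number and timing of measurements decide which comparison can be made, and sites may differ in which schedule they follow.

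Second, the text ties the last form to an event that happens after randomisation, namely reaching the last cycle. The article links early stopping to myelosuppression, which the interventions aim to reduce. Whether a patient has a final form may therefore depend on her arm. A comparison of final forms would then contrast selected patients, and it could miss a benefit that works by keeping patients on chemotherapy. An analysis rule written later cannot restore forms that were never collected.

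**Working it through.** The plan states no figure for this point, so there is none to reproduce. The check compares the two schedules, follows an early stopper through them, and then shows with assumed values what the loss could do.

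**1. Number of forms.** The text gives 3 for every regimen. Table 3 gives one per cycle plus baseline, or one fewer if the baseline form also serves as the form before cycle 1:

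| Planned cycles | Text | Table 3 |
|---|---|---|
| 4 | 3 | 4 to 5 |
| 6 | 3 | 6 to 7 |
| 8 | 3 | 8 to 9 |

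In the text, the questionnaire could be read as the TCM Constitution form alone, because that instrument is named just before. The conflict remains for that form, since Table 3 ticks its row at every cycle too.

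**2. A patient who stops early, under the text.**
- If the last cycle means the last planned cycle, that day never comes for her and there is no form.
- If it means the last cycle received, nobody knows on the day before that it will be the last, so the form cannot be scheduled.
- Table 3 has no quality-of-life tick after chemotherapy, so no later form fills the gap.
- Section {11b} continues collection as scheduled, but the schedule holds no quality-of-life time outside the cycles.
- She keeps her baseline form and, depending on when she stops, the mid-term form.

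**3. Patients left at the last time point.** With 154 per arm (Sample size {14}) and an assumed share d stopping early, 154 × (1 − d) remain:
- d = 5%: 146
- d = 10%: 139
- d = 15%: 131
- d = 20%: 123

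**4. What a comparison of completers can miss.** Let m be the mean of completers in an arm, d the share stopping, and g the deficit of stoppers against completers. The mean of the whole arm is (1 − d)m + d(m − g) = m − dg. The treated-minus-control difference missed by comparing completers is therefore

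d_C·g_C − d_T·g_T, where C is control and T a treated arm.

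With the same deficit g in both arms this is g(d_C − d_T). All values below are assumed:

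| d_C | d_T | g = 0.5 SD | g = 1.0 SD |
|---|---|---|---|
| 10% | 5% | 0.025 SD | 0.05 SD |
| 20% | 10% | 0.05 SD | 0.10 SD |
| 20% | 5% | 0.075 SD | 0.15 SD |

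Equal stopping rates remove the bias only if the deficits are equal as well. With 15% stopping in both arms, g_C = 1.0 SD and g_T = 0.5 SD, the missed difference is 0.15 × (1.0 − 0.5) = 0.075 SD.

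**5. A common time point.** Every regimen listed under Chemotherapy regimen plans at least four cycles: EC × 4 is the shortest fixed course, the open ranges start at 4, and FEC × 3 followed by T × 3 makes six. A comparison at planned cycle 4 is therefore defined for all of them.

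**The case against.** The strongest reply is that this is a wording mismatch on one secondary outcome. No primary outcome, sample size or error rate is touched. If Table 3 governs, early stoppers keep every form up to the time they stop. Scoring, missing-data handling and the choice of model belong in an analysis plan that is not shown. Much of this stands, and no complaint is made here about the absence of a missing-data method. What remains is what the article itself states: two incompatible schedules, and a final form that some patients cannot have.

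A reader might also infer more than the article supports:
- **That the patients most harmed by myelosuppression leave the quality-of-life comparison altogether.** They lose the last comparison and keep the earlier forms. That those lost are the most harmed is an inference: {6a} mentions dose reduction as well as discontinuation, dose-reduced patients who continue keep their forms, and {11b} also allows stopping at the participant's request.
- **That about 31 per arm (20% of 154) will lack the final form.** The 20% in Sample size {14} is a general drop rate, not a rate of stopping chemotherapy. Patients are also enrolled on the expectation that they complete the course.
- **That a range such as "taxanes (TC × 4–6 times, P × 4–6 times)" leaves the last cycle open for the individual patient.** The article lists ranges by regimen and does not say that the number is left unset for each patient at the start.

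**Conclusion.** The contradiction between the text and Table 3 is certain and needs no assumption. It is equally certain that, under the text, early stoppers have no final form and nothing later replaces it.

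That the last comparison is biased is a possibility. It requires stopping, or the deficit of stoppers, to differ by arm. The article's own rationale makes that plausible but supplies no rates. The size cannot be computed from the documents; the 0.025 to 0.15 SD range only shows the scale under assumed inputs. The direction is not settled either, since the calculation assumes that stoppers score worse than completers.

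The consequence is confined to quality of life and TCM Constitution, which are secondary outcomes. It should be corrected because forms not taken cannot be recovered.

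**What to change.** 1. State one schedule in both Secondary outcomes and Table 3. The every-cycle schedule of Table 3 is the natural choice, because it adds no visits during chemotherapy.
2. Index each form to planned cycle dates or to calendar time from randomisation, recorded at the start. Say how weekly paclitaxel is indexed.
3. Collect the forms at those times whether or not chemotherapy continues, unless the patient withdraws consent. Keeping forms tied to cycles actually given would not be enough, even with a mixed model, because a patient who stops before the comparison cycle would still have no form at that time.
4. Reconcile this with {11b} and {11c}, so that stopping treatment and withdrawing from data collection are clearly separate.
5. Compare arms at a fixed planned time that every listed regimen reaches, such as planned cycle 4, using all randomised patients with the baseline score as covariate.

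Cost: more than three questionnaires per patient, and a few forms outside chemotherapy visits. Trial status reports 218 of the planned 462 patients enrolled by 8 December 2019. Any of them followed under the three-times rule may lack some forms, so the plan should say which schedule was in use and from when.

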### Participant timeline {13}

The time schedule of enrolment, interventions, and assessments is as shown in Table 2.

**Table 2 Tab2:** TCM-related symptom assessment table

Symptoms	No effect	Partial improvement	Significant improvement
Abdominal distension or pain	0	1	2
Abnormal leucorrhea	0	1	2
Blurred vision	0	1	2
Chest tightness or pain	0	1	2
Chills	0	1	2
Constipation	0	1	2
Diarrhoea	0	1	2
Dizziness and tinnitus	0	1	2
Dreaminess	0	1	2
Dry bitter mouth	0	1	2
Dry eyes	0	1	2
Dysuria	0	1	2
Easy to catch a cold	0	1	2
Epigastric discomfort	0	1	2
Fatigue	0	1	2
Fingers and toes numb	0	1	2
Hair loss	0	1	2
Headache	0	1	2
Hectic fever	0	1	2
Heel pain	0	1	2
Insomnia	0	1	2
Irregular menstruation	0	1	2
Irritability	0	1	2
Itchy or sore throats	0	1	2
Loss of appetite	0	1	2
Lower limb pain	0	1	2
Memory loss	0	1	2
Nausea	0	1	2
Palpitations	0	1	2
Perspiration	0	1	2
Sticky mouth	0	1	2
Tasteless	0	1	2
Throat obstruction	0	1	2
Waist or knee pain	0	1	2

The efficacy is assessed on a scale of 3 levels. No improvement: No change in integral value after treatment or the integral value after treatment decreased by < 30% compare to that before treatment. Partial improvement: The integral value after treatment decreased by ≥ 30% compare to that before treatment. Significant improvement: The integral value after treatment decreased by ≥ 70% compare to that before treatment

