##### Course of treatment

Moxibustion starts from the 2nd day after chemotherapy and continued daily moxibustion until the day before the next cycle of chemotherapy. No moxibustion was given on the day of drug administration. The treatment course is completed 3 weeks after the end of the last chemotherapy. Daily self-moxibustion is carried out by the patient at home and is guided by Yueyang Hospital and Shanghai Acupuncture and Meridian Research Institute. Shanghai Research Institute of Acupuncture and Meridian will provide technical support for moxibustion.

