##### Rationale of TCM decoction

Post-operative CIM in breast cancer often causes fatigue, dizziness, and unwillingness to speak, palpitations, insomnia and dreaminess, spontaneous sweating and tachypnea, pale and enlarged tongue, weak pulses, etc. Although the concept of myelosuppression was not mentioned in ancient TCM, these clinical symptoms could be classified as a kind of “blood deficiency” and “consumptive diseases”. The treatment of CIM should, therefore, base on the concept of “tonifying the deficiencies” and “warming the consumptions”.

The *Astragalus*, *Codonopsis pilosula*, *Atractylodes macrocephala*, and *Poria cocos* in Wenshen Shengbai Decoction can tonify Spleen and support Qi and secure the postnatal condition, thus activating Qi and developing blood; *Adenophora tetraphylla* and *Lycium chinense* can nourish Yin and promote body fluid; *Epimedium, Cistanche deserticola, and Morinda officinalis* can tonify the kidney, regulate Chong Ren, and constrain the prenatal condition, thus enhancing the healthy Qi and resistance to pathogenic factors; *Curcuma zedoaria* and *Salvia chinensis* can promote blood circulation and detoxification and resolve phlegm; *Sophora flavescens* can clear away heat and dampness; *Rhizoma polygonati*, *Cornu cervi*, and *Psoralea corylifolia* can tonify kidney and fill the essence.

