#### Categorical variables

The frequency, relative number, and rate of the data will be calculated. If the data is not in order, the chi-square test or Fisher’s exact test is used to compare the difference between groups. If the data is in order, the rank-sum test is used instead.

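### The three-level TCM symptom response has no class for a worsened total, no rule for a zero baseline and overlapping upper classes, so a benefit that consists of less worsening is largely hidden

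*Protocol article*

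**What the plan says.** The symptom table under Participant timeline {13}, headed "TCM-related symptom assessment table", lists 34 symptoms, each scored 0, 1 or 2. The total therefore runs from 0 to 68. Its footnote sets three response levels:

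- The lowest level (no improvement) is defined as "No change in integral value after treatment or the integral value after treatment decreased by < 30% compare to that before treatment".
- The middle level (partial) is any fall of 30% or more from the starting total, with no upper limit given.
- The top level (significant) is any fall of 70% or more.

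No other section says what happens when the total rises or when it starts at zero. *Before treatment* is not tied to a visit. The Short-term efficacy section has the symptoms scored every 3 months, and the schedule of assessments has no row for this score.

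For context, prior systemic chemotherapy is an exclusion criterion. Under Course of treatment, "Moxibustion starts from the 2nd day after chemotherapy", and the decoction starts on the seventh day of each cycle. Under Rationale of TCM decoction, "Post-operative CIM in breast cancer often causes fatigue, dizziness, and unwillingness to speak, palpitations, insomnia and dreaminess". For ordered categories, the Categorical variables section says "If the data is in order, the rank-sum test is used instead".

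**The concern.** The rule grades improvement only, in a trial whose stated aim is partly prophylactic. Women start chemotherapy-naive and are then given chemotherapy in every arm. Fatigue, dizziness, palpitations, insomnia and dreaminess are in the symptom table and are named by the protocol as effects of chemotherapy-induced myelosuppression. The table also lists nausea, diarrhoea and loss of appetite, and the decoction is timed to avoid an acute gastrointestinal reaction. Many totals may therefore go up, and one plausible form of benefit is that they go up less.

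The three levels have little room for that. If an increase is put in the lowest level, a woman whose symptoms doubled counts the same as one who did not change or improved slightly. A rank-sum test on the levels cannot separate them. At stake are the sensitivity and interpretability of this short-term efficacy measure.

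**Working it through.** **1. Does the rule cover every outcome?** Let b be the total before and a the total after, both whole numbers from 0 to 68, with d = (b − a)/b. The printed levels are 0 ≤ d < 0.30, d ≥ 0.30 and d ≥ 0.70.

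- Pairs with b ≥ 1: 68 × 69 = 4,692.
- Increases (a > b): the sum of (68 − b) over b = 1 to 68, which is 68 × 67 / 2 = 2,278, or 2,278/4,692 = 49%. None has a level.
- No improvement: 735. Partial only: 938. Both partial and significant: 741. Check: 2,278 + 735 + 938 + 741 = 4,692.
- Pairs with b = 0: 69. Here d is undefined.

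These counts show where the rule is incomplete or overlapping. They are not expected shares of patients.

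**2. What the merge does to one patient.** Take b = 10. Final totals of 8 (d = 0.20) and 10 (d = 0) are no improvement. Final totals of 16 and 22 (d = −0.6 and −1.2) have no level and, if merged, join them. A treatment that turns 22 into 16 changes nothing on the scale. A final total of 3 (d = 0.70) meets two definitions at once.

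**3. How much is lost?** The protocol gives no mean, SD or expected change for this score, so every input here is assumed except the arm size: 154 less the protocol's 20% drop-out, 154 × 0.8 ≈ 123. All comparisons use two arms and a two-sided 0.05 level. Items are taken as scored by severity, and increases are merged into the lowest level.

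*Scenario set A.* Gamma baseline with mean 10, SD of change 8, treatment lowers the rise by 3 to 4 points. Rank-sum test on the levels; t-test on the change.

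| Mean rise in control | Three levels | Four levels (with worse) | Change in total |
|---|---|---|---|
| 10 | 32–63% | 48–77% | 83–97% |
| 5 | 53–80% | 65–90% | 81–97% |
| 0 (3-point effect) | 66% | 72% | 78% |

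The first row spans repeated runs. With a rise of 10, about 88% of control and 76–79% of treated patients worsen, and only 6% against 11–14% reach a 30% decrease.

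*Scenario set B.* Normal baseline with mean 10 and SD 3; treatment halves the mean rise. Rank-sum test on the levels and on the raw change.

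| Rise, control / treated | SD of change | Three levels | Raw change |
|---|---|---|---|
| 12 / 6 | 4 | 10% | about 100% |
| 10 / 5 | 4 | 36% | about 100% |
| 6 / 3 | 8 | 56% | 83% |
| 6 / 3 | 5 | 65% | about 100% |
| 8 / 4 | 6 | 76% | about 100% |
| 10 / 5 | 6 | 83% | about 100% |

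In set B, 76–99.8% of control and 62–91% of treated patients have an increased total. The three levels have less power than the change in total in every scenario of both sets. The gap is widest when nearly everyone worsens.

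**The case against.** **The score is minor.** It is in neither the primary nor the secondary outcome list and appears only under Short-term efficacy. Worsening can also be captured by CTCAE-graded adverse effects, ECOG PS and the EORTC questionnaires. This stands, and it limits the importance of the point.

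**A risen total is plainly no improvement.** That is the natural reading. A reader might infer that worsened patients would drop out of the comparison, which would select on a post-randomisation outcome. The protocol does not say so, and its ITT dataset includes all eligible participants. What remains is a loss of information, not a demonstrated selection bias.

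**The baseline is not stated to be before chemotherapy.** A reader might infer that it is. The protocol does not define the term, and a score just before the first moxibustion or decoction would come after chemotherapy had begun. The final score may also follow some recovery, since moxibustion ends 3 weeks after the last chemotherapy. A pre-chemotherapy visit is the likeliest anchor because the control arm has no study treatment to anchor to, but that is an inference. The gap in the rule exists on either reading, and the ordering of power held even with no mean rise.

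**The table as printed scores the other way.** Its column heads run from no effect (0) to significant improvement (2), while the footnote treats a falling total as improvement. That contradiction is a separate defect and must be resolved first. The missing class is still missing after the items are rescored as severity.

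**Continuous methods are already in the plan.** The Continuous variables section could be applied to the raw total. The article does not assign this score to it; the footnote assesses efficacy on the three levels.

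**Conclusion.** The point holds in a limited form. The rule is incomplete for an increase, undefined for a zero baseline, and its middle level contains its top level; all three can be checked on the page. On the natural reading, a benefit that consists of less worsening is largely hidden. A reader might go further and say that the rule cannot show such a benefit. The figures do not support that: limiting the rise also carries some patients across the 30% threshold, so power on three levels was about 10–83% across the scenarios, against about 78–100% on the change in total. The direction of the loss was the same in every scenario. Its size rests on assumed baseline, rise, SD and effect, on two arms where the trial has three, and on severity scoring of the items. No primary or listed secondary outcome depends on the rule, so this is worth correcting but does not threaten the main results.

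**What to change.** 1. Resolve the item scale first, so that a higher total means worse symptoms.
2. State which visit is *before treatment* and which is *after treatment*, the same for all three arms.
3. Make the between-arm comparison of change in raw total the main analysis of this score, using the methods under Continuous variables (one-way ANOVA or Kruskal-Wallis).
4. If classes are also reported, use four exclusive ordered classes: worse (any increase) < no improvement (no change or a decrease below 30%) < partial (decrease of 30% to below 70%) < significant (decrease of 70% or more). Adding a worse class alone recovers only part of the loss (48–77% against 83–97% with a rise of 10), which is why step 3 comes first.
5. For a zero baseline, class a positive later total as worse and a zero later total as no improvement.

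The cost is a few lines in the footnote and the analysis text. No new data are needed, since the rule already presumes a score before and after treatment. The small downside is a departure from the three-level rule, which can be kept as a collapsed secondary table with increases shown as no improvement. The change should be made before between-arm data on this score are examined.
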